# Comparing two implementation strategies for implementing and sustaining a case management practice serving homeless-experienced veterans: a protocol for a type 3 hybrid cluster-randomized trial

**DOI:** 10.1186/s13012-022-01236-1

**Published:** 2022-10-03

**Keywords:** Homeless veterans, Case management, Replicating effective programs, Facilitation, Implementation science

## Abstract

**Background:**

The Veterans Health Administration (VA) Grant and Per Diem case management “aftercare” program provides 6 months of case management for homeless-experienced veterans (HEVs) undergoing housing transitions. To standardize and improve aftercare services, we will implement critical time intervention (CTI), an evidence-based, structured, and time-limited case management practice. We will use two strategies to support the implementation and sustainment of CTI at 32 aftercare sites, conduct a mixed-methods evaluation of this implementation initiative, and generate a business case analysis and implementation playbook to support the continued spread and sustainment of CTI in aftercare.

**Methods:**

We will use the Replicating Effective Programs (REP) implementation strategy to support CTI implementation at 32 sites selected by our partners. Half (*n*=16) of these sites will also receive 9 months of external facilitation (EF, enhanced REP). We will conduct a type 3 hybrid cluster-randomized trial to compare the impacts of REP versus enhanced REP. We will cluster potential sites into three implementation cohorts staggered in 9-month intervals. Within each cohort, we will use permuted block randomization to balance key site characteristics among sites receiving REP versus enhanced REP; sites will not be blinded to their assigned strategy. We will use mixed methods to assess the impacts of the implementation strategies. As fidelity to CTI influences its effectiveness, fidelity to CTI is our primary outcome, followed by sustainment, quality metrics, and costs. We hypothesize that enhanced REP will have higher costs than REP alone, but will result in stronger CTI fidelity, sustainment, and quality metrics, leading to a business case for enhanced REP. This work will lead to products that will support our partners in spreading and sustaining CTI in aftercare.

**Discussion:**

Implementing CTI within aftercare holds the potential to enhance HEVs’ housing and health outcomes. Understanding effective strategies to support CTI implementation could assist with a larger CTI roll-out within aftercare and support the implementation of other case management practices within and outside VA.

**Trial registration:**

This project was registered with ClinicalTrials.gov as “Implementing and sustaining Critical Time Intervention in case management programs for homeless-experienced Veterans.” Trial registration NCT05312229, registered April 4, 2022.

Contributions to the literature
This protocol presents a pragmatic example of implementing a complex case management practice in diverse community-based organizational settings.This trial integrates a cluster-randomized design and mixed-methods evaluation to compare the impacts of two implementation strategies on the implementation and sustainment of an evidence-based case management practice.This protocol describes the development of products (i.e., business case analysis and implementation playbook) that can be used by policy partners to support the continued spread and sustainment of a complex case management practice in diverse community-based organizations.

## Background

Compared to housed veterans, homeless-experienced veterans (HEVs) have profound health disparities, including high rates of medical illness, psychiatric problems, and substance use disorders (SUDs) [1]. With a substantial investment of VA resources, veteran homelessness decreased by 50% (from 73,367 to 37,252) from 2009 to 2020 [2]. Veterans who remain homeless despite these services are extraordinarily vulnerable; 40% are unsheltered, living outdoors or in other places not intended for human habitation [2]. To further the VA’s goal of ending veteran homelessness [3], there is a pressing need to identify strategies that support the scale-up, spread, and sustainment of evidence-based practices (EBPs) across the range of programs that serve HEVs.

The Grant and Per Diem (GPD) program is a cornerstone of the VA’s plan to end veteran homelessness. Operated by VA’s community partners, this program provides transitional housing (for ≤24 months) and supportive services for HEVs. Many HEVs transitions from GPD sites into independent housing; the initial phase of this transition can be challenging and associated with adverse outcomes, including returns to homelessness and hospitalizations [4]. Until recently, GPD case management ceased during the transition from GPDs, leaving HEVs without structured case management unless they entered VA’s permanent supportive housing program. In March 2019, under direction from Congress, VA awarded $30 million to 128 GPD sites to provide 6 months of case management (in the GPD case management “aftercare” program) for HEVs transitioning to independent living and not otherwise receiving case management. However, no specific case management paradigm was required in aftercare, resulting in site-level practice variation.

GPD National Program Office policy leaders identified critical time intervention (CTI) as an evidence-based, structured, and time-limited case management model that—if implemented nationally—would standardize and improve aftercare case management. There are five randomized controlled trials (RCTs) [5–8] and a systematic review [9] demonstrating that CTI effectively improves housing and decreases hospitalizations among homeless-experienced adults. Moreover, CTI was successfully implemented in 8 VA facilities for HEVs with serious mental illness, suggesting it is feasible and appropriate for VA scale-up and spread. CTI is also well-aligned with aftercare, which was designed to improve housing stability among HEVs undergoing housing transitions. However, implementing EBPs in community-based organizations serving HEVs brings challenges [10, 11].

This paper describes the protocol for the Housing Transitions Quality Enhancement Research Initiative (QUERI), which will implement CTI across 32 aftercare sites nationally and compare the impacts of two implementation strategies on effectiveness and implementation outcomes. To implement and sustain CTI, we will use the Replicating Effective Programs (REP) implementation bundle to enable sites to achieve fidelity to CTI’s core components, while accommodating adaptations to fit the diversity of aftercare contexts. REP includes EBP packaging, staff training and technical assistance, process evaluation and feedback, and ongoing maintenance support [12]. Half of these sites (*n*=16) will receive an “enhanced REP” bundle in which REP is augmented by 9 months of EF, a process of providing tailored support for providers and leaders to adopt and incorporate EBPs into routine care. We will provide our partners with evidence regarding the comparative impacts and costs of REP vs. enhanced REP for CTI implementation and sustainment across diverse aftercare contexts, including sites with quality gaps.

Partnered with national and regional leaders in VA homeless services, this project’s Specific Aims are to [1] use REP and enhanced REP to support the implementation and sustainment of CTI in 32 aftercare sites [2]; compare, in a type 3 hybrid implementation-effectiveness trial [13], the impacts of REP vs. enhanced REP on CTI fidelity and sustainment, quality metrics (focused on housing stability and hospitalizations), and costs and return-on-investment; and [3] generate two key products for program partners—a business case analysis and an implementation playbook—to support continued spread and sustainment of CTI in the aftercare program.

## Methods

### Overview

We hypothesized that enhanced REP will have higher implementation costs than REP, but enable increased tailoring to local contexts that results in stronger CTI implementation and effectiveness, supporting a business case for enhanced REP. To test this hypothesis, we will use a type 3 hybrid implementation-effectiveness trial [13]; this design tests the impacts of implementation strategies while gathering data regarding an EBP’s impacts on clinical outcomes. Specifically, we will compare the impacts of REP versus enhanced REP on CTI implementation and sustainment, while observing CTI’s effectiveness on housing and health outcomes. In a cluster randomized design, we will assign 32 aftercare sites to REP (*n*=16) versus enhanced REP (*n*=16), clustering sites in three implementation cohorts staggered in 9-month intervals.

### Conceptual framework

Housing Transitions QUERI is built on the conceptual framework illustrated in Fig. 1, which draws upon recommendations by Smith et al. [14] for specifying the logic in implementation planning and evaluation. We used the Consolidated Framework for Implementation Research (CFIR) [15], which draws upon theory and constructs from implementation science to describe contextual factors across five domains (perceived intervention characteristics, outer context, inner setting, characteristics of individuals, and implementation processes) associated with CTI implementation outcomes.

**Fig. 1 Fig1:**
[figure not shown]
Conceptual framework [15, 16]

### Critical time intervention (CTI)

In CTI, clients (e.g., HEVs) are assigned to case managers (“CTI specialists”) who link them to services and resources aligned with their housing and other goals. Core components of CTI (Fig. 2) include the CTI specialist who delivers field-based services (e.g., home visits) that help clients mobilize resources and support. The background and training of CTI specialists range from peer providers with lived expertise in homelessness to master’s level clinicians (e.g., social workers). CTI is delivered over 6 to 9 months in three time-limited phases of decreasing intensity: [1] transition to the community (development of a care plan with salient goals), [2] try out (clients test problem-solving skills using plans established with their CTI specialist), and [2] transfer of care (care transition from CTI specialist to a longitudinal care team). Services focus on housing stability, personal goals, and building a support network. The Template for Intervention Description and Replication (TIDiER) checklist is available as supplemental material.

**Fig. 2 Fig2:**
[figure not shown]
Core components of CTI

### CTI implementation pilot

Housing Transitions QUERI builds on a 1-year implementation pilot in which we developed resources and processes for CTI training and technical assistance (TA) and external facilitation that were piloted and refined at four aftercare sites. We also identified outcome measures for future evaluation. To this end, we formed a virtual stakeholder workgroup comprised of two CTI expert trainers, a faculty consultant from a university-based center with CTI expertise, a VA social worker who served as the “liaison” to the four pilot sites, and a peer provider with professional and lived expertise in GPD programs.

We drew upon this workgroup to tailor a 6-month version of CTI that was previously implemented in Connecticut-based homeless programs [17]. We made practice adaptations to reflect the aftercare context and augmented anonymized cases presented in the training and TA materials to reflect the social circumstances, functioning, and diagnoses of HEVs in aftercare. We made additional adaptations in response to precautions imposed by the coronavirus disease 2019 (COVID-19) pandemic and ensured that all training and TA could be delivered virtually. We also developed an online toolkit [18] with clinical resources, recorded trainings, a CTI manual, and training and TA slide decks.

Next, we pilot-tested this adapted training and TA package (Table 1) with aftercare case managers, supervisors, and our VA social work liaison. First, initial CTI training was delivered in six synchronous videoconferences by national leaders in training and consultation for case managers serving homeless-experienced adults. Next, we initiated a monthly community of practice sessions, i.e., 1-hour discussions to deepen knowledge and expertise in CTI; these sessions included a presentation from the community of practice leader (a social worker on our team) or guest speaker, followed by a moderated discussion among aftercare staff. We also offered individual, on-demand, 30-min case consultations to aftercare staff with a CTI-trained clinician expert on our team.

**Table 1 Tab1:** CTI training and technical assistance (TA) package tailored in the Housing Transitions QUERI implementation pilot

Training/TA component	When is the component delivered?
Six session initial CTI training delivered via synchronous videoconference (2 h/week for 6 weeks)	Once, at the start of CTI implementation, for all aftercare case managers and supervisors
Online CTI toolkit, including recorded training sessions, the CTI manual, clinical templates and tools, and relevant resources	As needed by any aftercare case manager or supervisor
On-demand case consultation process with a CTI expert via telephone or videoconference (30 min/consultation)	As needed—requested by any aftercare case manager or supervisor, up to once/month per aftercare site
Community of practice sessions delivered via synchronous videoconference (1 h/session)	Monthly for 6 months, starting the month after the 6-session initial CTI training is completed
Listserv to facilitate sharing of clinical practices and anonymized case discussion among aftercare case managers and supervisors across sites	As needed by any aftercare case manager or supervisor
CTI booster sessions delivered via synchronous videoconference (1 h/training)	Every 3 months, beginning 9 months after the start of CTI implementation

Last, we developed and pilot-tested EF materials and processes. EF is a flexible implementation strategy involving deliberate and interactive problem-solving and support for providers to implement EBPs. In our pilot, a facilitator trained in CTI and facilitation provided tailored support that built the sites’ organizational capacity to implement CTI and empowered case managers to enact systems-based change toward CTI implementation [19]. After each session, the facilitator completed a templated form to summarize the call, engage in self-reflection, delineate facilitation strategies used, and highlight barriers faced in employing these strategies. Data from these forms were used to create a CTI facilitation guide.

Qualitative data from this pilot suggested that most aftercare case managers were highly satisfied with CTI and comfortable using this practice with HEVs. Post-training, case managers reported that CTI was acceptable and credible, with strong data for its effectiveness. Though case managers struggled with the time-limited (6 months) aftercare duration, there was consensus that CTI was a compatible and useful model in this context. Funding was obtained to proceed to a 32-site national implementation and evaluation.

### Implementation strategy: Replicating Effective Programs (REP)

Housing Transitions QUERI will use REP at 32 aftercare sites to implement CTI. REP is a bundle of implementation strategies with a strong evidence base and precedent of feasibility within VA [20, 21]. REP uses stakeholder input to facilitate packaging, training, and TA of EBPs; we selected REP because it resembles “usual care” mental health EBP rollouts in VA. Our use of REP is intended to enhance case managers’ CTI skills and clinical competency, thereby strengthening CTI fidelity and sustainment. REP is particularly well-suited for CTI implementation; research shows that adapting and packaging CTI and its trainings and TA for program and population contexts, using stakeholder input, is critical for effective, high-fidelity implementation [22].

Figure 3 depicts REP’s phases and each phase’s products, specified for this project. Phases one and two (“pre-conditions and “pre-implementation”) were completed in our implementation pilot. Phases three and four comprise the focus of this protocol. Phase three (“implementation”) will encompass national delivery of the CTI package to 32 sites, with iterative refinement informed by our implementation evaluation. Phase four (“maintenance and evolution”) will include booster sessions, modeled on prior CTI rollouts. This final phase of REP also includes assessing financial factors and organizational changes needed for CTI sustainment.

**Fig. 3 Fig3:**
[figure not shown]
Replicating effective programs (REP) specified for CTI implementation in the aftercare program

Of note, though REP enables stakeholder-informed CTI training and TA, it does not include site-level support beyond on-demand case consultation. Aftercare sites that receive only REP will not work with our team to develop site-level implementation support. As such, REP alone does not provide support specifically tailored to local contexts.

### Implementation strategy: enhanced REP

In addition to REP, 16 of 32 aftercare sites will receive EF (enhanced REP), which will provide these sites with support tailored to their local contexts. Compared to REP alone, REP enhanced with EF is a higher intensity and higher cost strategy to support CTI implementation. Figure 4 depicts REP versus enhanced REP activities as experienced by sites. We hypothesize that enhancing REP with EF will improve CTI fidelity and sustainment by catalyzing case management activation and organizational changes.

**Fig. 4 Fig4:**
[figure not shown]
REP vs. enhanced REP, as experienced by sites

We selected EF to enhance REP because it is a powerful tool, based on organizational theory, that can assist with organizational change by addressing site-specific implementation barriers. In our pilot, we found that tailored support for site-specific challenges was important for CTI implementation. In Housing Transitions QUERI, EF will be delivered by facilitators who are social workers trained in CTI and facilitation. EF sessions (30 min/week videoconferences) will begin within 2 weeks of aftercare staff completing initial CTI training and continue through month 9 of CTI implementation. The content of sessions will vary by sites’ needs and contextual factors; facilitators will employ the guide developed in our pilot, using real-time data and quality improvement techniques to identify steps that sites can follow to implement CTI.

Throughout, facilitators will engage in the implementation and support-oriented activities (Table 2). Though facilitators are trained in CTI, they do not provide CTI clinical support or case management training; clinical and training needs are referred to the REP team.

**Table 2 Tab2:** Sample external facilitation activities

Implementation-oriented activities	Support-oriented activities
• Identify CTI implementation challenges and apply rapid-cycle improvement processes to address these challenges • Use VA administrative data to rapidly monitor outcomes (e.g., service use) of Veterans on a case manager’s caseload and provide feedback to aftercare staff • Educate aftercare staff and VA aftercare liaisons and identify key VA and community resources • Develop a site-specific CTI implementation plan	• Build relationships with aftercare staff • Encourage CTI practice and implementation • Educate aftercare staff on external facilitation, including its benefits and roles • Engage with and develop a plan to routinely update local change agents and other key stakeholders on CTI implementation • Ensure resources and personnel are available to grow and/or adapt CTI as needed

### Participating sites

Our partners at the GPD National Program Office identified 7 priority VA regions (Veterans Integrated Services Networks [VISNs]) for CTI implementation in aftercare. We will engage with VA homeless program leaders in these VISNs, and their associated VA facilities, to identify 32 aftercare sites across three cohorts, with 10–11 sites per cohort. Sites for each cohort will be identified in the 3 months prior to cohorts’ implementation initiation, based on sites self-identifying as being ready for implementation. Of note, our sample size (32 sites) was pre-determined by our funder.

### Study design

We plan a type 3 hybrid implementation-effectiveness trial [13], registered as NCT05312229 on April 4, 2022, and determined to be non-research by VA’s Central Institutional Review Board. Given distinct leadership, staffing, and policies by site, and the high likelihood of contamination among case managers within sites, cluster randomization will occur at the site level. Within each cohort, the implementation team will use permuted block randomization—with geographic setting (urban, suburban, and rural) and number of case managers (a proxy for site size and resources) as stratification factors—to balance these factors among sites receiving REP versus enhanced REP. Figure 5 depicts a Consolidated Standards of Reporting Trials (CONSORT) flow diagram of our comparison groups. We will also use the stratification factors to match each of the 32 implementation sites to a control aftercare site not implementing CTI. Data from control sites will be used to assess selected quality metrics and costs of CTI as implemented. The CONSORT 2010 checklist of information for randomized controlled trials is available as supplemental material.

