**Fig. 5 Fig5:**
[figure not shown]
Consort diagram

We will use a staggered parallel cluster randomized design [23] (Fig. 6), with cohorts initiating REP and enhanced REP in 9-month intervals. Staggering is necessary to create cohorts sized for optimal training and EF within project resources. Sites are not blinded to implementation strategy assignments.

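### Permuted blocks stratified by setting and site size within cohorts of 10–11 sites do not reliably deliver the stated 16/16 split and give only limited balance on the two factors

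*Protocol article*

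**What the plan says.** Under Participating sites, the team works "to identify 32 aftercare sites across three cohorts, with 10–11 sites per cohort". The number 32 was set by the funder. The same section says: "Sites for each cohort will be identified in the 3 months prior to cohorts’ implementation initiation".

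Under Study design, the article states: "Within each cohort, the implementation team will use permuted block randomization". The factors are "geographic setting (urban, suburban, and rural) and number of case managers (a proxy for site size and resources) as stratification factors", and the purpose is "to balance these factors among sites receiving REP versus enhanced REP". After Fig. 5 it adds: "Staggering is necessary to create cohorts sized for optimal training and EF within project resources".

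The Overview fixes the result of the allocation: "we will assign 32 aftercare sites to REP (*n*=16) versus enhanced REP (*n*=16"). The abstract, the Background and the section on enhanced REP repeat the figure of 16 sites.

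Under CTI fidelity, the primary outcome is a site-level score at 12 months, compared between the two strategies with a t-test. No adjustment for cohort, setting or site size is mentioned there.

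The article does not give the block size, the categories for number of case managers, whether the two factors are fully crossed, or how incomplete blocks are handled.

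**The concern.** Permuted blocks hold the arms equal only where blocks are filled. Cohort, setting and size together cut 32 sites into many small cells, and each cell with an odd number of sites leaves one site to chance. These leftovers add up across cells, because no stated rule links one cell or one cohort to another. An 11-site cohort cannot split evenly in any case, so 16/16 needs a planned offset between the two cohorts of 11.

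Two things are at stake. The stated split may not occur. More importantly, the arms may differ in setting or size, which is what the stratification is there to prevent. If either factor predicts fidelity, that difference enters an unadjusted comparison of 32 sites.

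**Working it through.** **Inputs from the article.** 32 sites in three cohorts of 10–11, which forces 11 + 11 + 10 = 32; three settings; intended split 16/16.

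**Assumptions, because the article gives no figures.** Setting and size are fully crossed within cohort. Size has k = 2 or 3 levels, assigned at random. Blocks are of 2 or 4. The setting mix is even, 50/25/25 or 60/25/15.

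**Step 1, sites per cell.** Cells per cohort = 3 × k.
- k = 2: 6 cells per cohort, 10/6 = 1.67 to 11/6 = 1.83 sites per cell; overall 32/18 = 1.78.
- k = 3: 9 cells per cohort, 10/9 = 1.11 to 11/9 = 1.22; overall 32/27 = 1.19.

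The mean is below two for any k of 2 or more.

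**Step 2, the 16/16 split, closed-form check for blocks of 2.** Each odd-sized cell adds +1 or −1 to the difference between arms. With m odd cells, P(16/16) = C(m, m/2)/2^m; m must be even because 32 is even. The simulation gives about 2.95 odd cells per cohort for k = 2 (even mix), so m is about 8.9, and 4.23 for k = 3, so m is about 12.7.
- m = 8: 70/256 = 0.27
- m = 10: 252/1024 = 0.25
- m = 12: 924/4096 = 0.23

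**Step 3, simulation (4,000 trials per scenario, ranges over the assumed setting mixes).**

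| Scheme | Exactly 16/16 | 18/14 or worse |
|---|---|---|
| Crossed strata, blocks of 2, k = 2 | 26–28% | about 30% |
| Crossed strata, blocks of 2, k = 3 | 23% | 36–40% |
| Crossed strata, blocks of 4, k = 2 | 19–21% | 41–46% |
| Crossed strata, blocks of 4, k = 3 | 17–19% | 48–50% |
| Cohort-only, blocks of 2 | 48–50% | 0% |
| Simple randomization | 14% | 60% |

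The blocks-of-2 rows agree with Step 2. The simple-randomization row agrees with C(32,16)/2^32 = 0.14. Cohort-only blocks of 2 give 16/16 half the time because only the two odd sites of the 11-site cohorts are left to chance; otherwise the split is 17/15.

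**Step 4, factor balance.** The measure is the mean of the largest difference between arms, in sites, within any level of the factor (even and 60/25/15 mixes).

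| Scheme | Setting, k = 2 | Size, k = 2 | Setting, k = 3 | Size, k = 3 |
|---|---|---|---|---|
| Crossed strata, blocks of 2 | 2.2 | 2.2–2.3 | 2.6–2.7 | 2.5–2.7 |
| Crossed strata, blocks of 4 | 2.8–3.0 | 2.9–3.1 | 3.3–3.5 | 3.3–3.5 |
| Cohort-only, blocks of 2 | 3.1–3.3 | 2.7 | 3.1–3.3 | 3.3 |
| Simple randomization | 4.4 | 4.5 | 4.3–4.4 | 4.3 |

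Blocks of 2 keep a real gain over cohort-only blocks. With blocks of 4 the gain on setting is small at k = 2 and gone at k = 3, and there is essentially none on size.

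**Step 5, precision cost of unequal arms.** Relative efficiency = 4·n1·n2/32².
- 17/15: 1020/1024 = 0.996
- 18/14: 1008/1024 = 0.98
- 20/12: 960/1024 = 0.94

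**The case against.** The strongest reply is that the article names a method and two factors and leaves the details to a fuller document. Block size, size categories and the handling of remainders may be fixed there. Each cohort's sites are identified before it starts, so the team could pair odd cells or offset the two 11-site cohorts and reach 16/16. This stands in part: the omission of those details is no fault, and full crossing is the conventional reading, not a stated one. It does not remove the point, because the method as named falls short at both block sizes and at two or three size levels. Reaching 16/16 needs a rule beyond it.

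A reader might infer three stronger things that the documents do not support.

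- That the stratification fails at its purpose. It does not: every crossed scenario balances the factors better than simple randomization, and blocks of 2 also beat cohort-only blocks.
- That unequal arms materially weaken the trial. Step 5 shows they do not.
- That uneven cohorts would exceed the facilitation capacity. The article says that cohorts are sized for training and facilitation within resources, but states no maximum number of facilitated sites. A 7/4 split in place of 6/5 may mean one more facilitated site, and the surplus is as likely to fall in the REP arm.

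**Conclusion.** The point holds in a limited form. As described and conventionally read, the scheme does not reliably produce the 16/16 split that the article states: about 17–28% of trials reach it, and about 30–50% end at 18/14 or worse. Balance on setting and size is limited and depends on a block size that the article does not give. With the primary t-test described without adjustment, leftover imbalance in a factor related to fidelity would carry into the estimate.

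The percentages rest on full crossing, two or three size levels and assumed setting mixes. The figure of fewer than two sites per cell rests only on crossing and at least two size levels. This is an avoidable weakness worth considering, not a threat to the validity of the trial.

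**What to change.** For each cohort not yet randomized, wait until its sites are confirmed and allocate them all at once. Fix the cohort splits so that they sum to 16/16, for example 6/5, 5/6 and 5/5. List the possible allocations: C(11,5) = 462 for a cohort of 11 and C(10,5) = 252 for a cohort of 10. Keep those that are well balanced on setting and number of case managers, counting earlier cohorts, and draw one at random. If a cohort has already been randomized, choose the remaining splits to bring the total as close to 16/16 as possible.

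Replace the plain t-test with a site-level comparison of fidelity adjusted for cohort, setting and number of case managers.

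The cost is a short script and a few sentences in the protocol. The cohort's sites must be confirmed before the draw. The adjustment uses five degrees of freedom if number of case managers enters as one linear term (2 for cohort, 2 for setting, 1 for size), leaving 25 in place of 30.
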